# Evaluation of a technology-enhanced, integrated community health and wellness program for seniors (HWePS): protocol of a non-randomized comparison trial

**DOI:** 10.1186/s12889-022-14921-z

**Published:** 2023-01-05

**Keywords:** Health equity, Integrated community care model, Personalized care, Health literacy, Digital technologies, Geriatric care model

## Abstract

**Background:**

Healthy aging for all in the community is a shared public health agenda for countries with aging populations, but there is a lack of empirical evidence on community-wide preventive models that promote the health of older people residing in socially-disadvantaged communities. The Health and Wellness Program for Seniors (HWePS) is a technology-enhanced, multi-level, integrated health equity intervention model. This study evaluates the effect of the HWePS on the health and well-being of older adults residing in urban, low-income communities.

**Methods/design:**

HWePS is a prospective, non-randomized comparison trial conducted in an intervention and a control neighborhood (*dong*) in Seoul, South Korea, over 12 months. Older people who reside in the small areas and meet the inclusion/exclusion criteria are eligible to participate. The multi-level, multi-faceted HWePS intervention is a preventive community care model for older residents guided by the expanded chronic care model, the comprehensive health literacy intervention model, and the Systems for Person-centered Elder Care model along with health equity frameworks. HWePS consists of four components: a health literacy intervention based on individual and community needs assessments, personalized (self-)care management featuring nurse coaching and peer support, a healthy-living and healthy-aging community initiative, and information and communication technology (ICT) systems. The primary outcomes are self-reported health and health-related quality of life. Outcome assessors and data analysts are blinded to group assignment. Process evaluation will be also conducted.

**Discussion:**

As a multi-level health equity project, HWePS has adopted a novel study design that simultaneously targets individual- and community-level factors known to contribute to health inequality in later life in the community. The study will provide insights into the effectiveness and implementation process of an integrated, multi-level, preventive community care model, which in turn can help improve the health outcomes of older residents and reduce disparities in underserved urban communities.

**Trial registration:**

ISRCTN29103760. Registered 2 September 2021, https://www.isrctn.com/ISRCTN29103760

## Background

Healthy aging is a widely accepted common goal of most countries with aging populations, regardless of income level. The proportion of older adults in the world’s population is expected to reach 16% by 2050 [1] and a majority of these older people are also expected to reside in urban communities [2]. Various policy efforts to promote healthy aging have been made at the country and international levels [3, 4]. Often overlooked, however, is that opportunities for healthy aging are unequally distributed within and between countries [3]. Another gap in the healthy aging intervention literature is that most interventions target health behaviors at the individual level only [5, 6], despite the potential impacts of the communities where the individuals reside. Yet another gap is that healthy aging interventions and programs often target those with specific diseases, or risks, for whom the intervention effects can be clearer; the generalizability of those studies is limited [7]. Together, these gaps have resulted in a lack of evidence on community-wide preventive models promoting healthy aging for relatively healthy community-dwelling older adults and, in particular, those who are socially disadvantaged.

Health equity is a critical goal of public health policy and practice. Beyond mere surveillance and monitoring of health disparities, heath equity interventions aiming to reduce and/or eliminate health disparities have been designed and tested [8, 9]. However, these interventions often fall short of achieving health equity, partly attributable to gaps in knowledge and translation [10]. Interventions are often focused on downstream—rather than upstream—social determinants of health [11, 12]. A lack of understanding of the pathways through which social factors influence health is another critical gap. Multi-level, population-tailored approaches along with community engagement have been key recommendations for disparity studies in public health and intervention science [10, 13].

To address such gaps in the healthy aging and health disparity literature, public health interventions promoting health equity for community-dwelling older adults are needed. This study aims to develop and evaluate an integrated health equity intervention promoting the health and wellness of older people in an urban, low-income community in Seoul, South Korea (henceforth *Korea*). Korea is an East Asian country experiencing the most rapid population aging and the highest elderly poverty rate among the OECD countries [14]. As a consequence of rapid urbanization over the last 30–40 years, there is a large number of urban, lower-income elderly, and meeting their health and care needs is essential to promoting healthy aging for all. Seoul, the capital of Korea, is a mega-city with a population of 9.9 million in 2022, among which about 17.2% are older adults and about 350,000 are older adults living alone [15]. The city health department places public health nurses in each of the approximately 420 community service centers in the city [16], a bold step to increase access to preventive public health services for the poor and/or older residents in local communities and a move that has now been benchmarked by many other provinces in Korea. Yet unwarranted variations still exist in health care access and outcomes across communities in Seoul and across the country, and such gaps have not been easily narrowed [17]. Under the COVID-19 pandemic, it is also essential to improve access to care and to protect the health and well-being of older people in low-income communities, where infection rates and the negative impacts of service closures related to social distancing measures are higher compared to their counterparts [18].

### Theoretical rationale

The Health and Wellness Program for Seniors (HWePS) is a technology-enhanced, multi-level, integrated health equity intervention model that aims to promote the health and wellness of older people in an urban, low-income community. As a small-area, public-health equity program (intervention), the HWePS was designed based on several theoretical and conceptual models. The components and process of the HWePS intervention are guided by the expanded chronic care model (ECCM) [19], the Systems for Person-centered Elder Care (SPEC) model [20], and the comprehensive health literacy (HL) intervention model [21] as well as the health inequality models described below. Guided by the Commission on Social Determinants of Health (CSDH) conceptual framework [22], the intervention assumes exposure and vulnerability to health-comprising conditions vary by social status, a structural determinant of heath (SDH) inequalities; it also hypothesizes that a health system is not an SDH in itself but rather an important mediator that can change the health and wellness of people through access to care and intersectoral action.

The Bay Area Regional Health Inequities Initiative’s (BARHII’s) public health framework for reducing health inequalities is a decision-making framework for the California Department of Public Health [23]. In order to address heath inequalities, the conceptual framework emphasizes the focus of public health practices should move toward living conditions as well as institutional and social inequalities (middle and upstream determinants), beyond the traditional medical model-based practice mainly focusing on individual risk behaviors and disease and injury (downstream determinants). Underpinned by the emerging public health practice paradigm in BARHII’s framework, the HWePS is designed to improve living conditions, in particular the health and social service environment, by creating a healthy living and healthy aging environment at the neighborhood (small-area) level. The living environment, according to BARHII’s framework, has a critical role as a modifier to reduce the impacts of upstream factors of inequalities on individual health. A healthy-living, healthy-aging initiative including a wide range of activities for community capacity-building and civil engagement is a critical component of the HWePS intervention. The activities were mainly selected based on suggestions and requests from older residents and community leaders in collaboration with public health officials, community service centers, and NGOs, with available resources and programs in the Jungnang-gu (district) and also, more broadly, the city of Seoul.

Along with this community-level healthy aging initiative, the HWePS addresses determinants of health inequality at the individual and interpersonal (social) levels, which assumes each older adult has unique needs and preferences in developing their optimal healthy aging trajectory [3]. A personalized care-management program featuring care planning and coaching that supports each older person in maximizing knowledge, skills, and competency for self-care, is essential for improving health and well-being in later life.

The individual-level intervention components of the HWePS were designed by adopting and modifying the components and process of the Systems for Person-centered Elder Care (SPEC) [20, 24, 25]. SPEC is an integrated geriatric care model, developed and tested at nursing homes in Korea, that significantly improved quality of care for frail older adults with multiple chronic illness [20]. The geriatric assessment-based care planning in the SPEC is also a vital component of the individual-level intervention in the HWePS. The participants and scope of the SPEC’s interdisciplinary case-conferences and care-coordination have been expanded for the community-based, civil-engaged HWePS intervention. ICT tools, another component of the SPEC model, are also a core component of the HWePS model. The expanded chronic care model [19], which emphasizes the importance of community capacity-building for health promotion beyond traditional health systems and institutions, not only guided the further development and tailoring of the SPEC intervention model developed under the chronic care model [26] but also is the theoretical framework of the community-based HWePS.

Lastly, the HWePS was guided by the comprehensive health literacy (HL) intervention model emphasizing the critical role of health literacy in reducing heath inequalities and promoting healthy aging [21]. The HL model suggests interventions should target the following five factors [21]: the context of the individual, via interventions strengthening community social support (e.g., family, peers, communities); the individual, via interventions improving each person’s low heath literacy (e.g., person-centered capacity-building and self-management); the interaction between the individual and the heath system, via interventions to improve communication between individuals and health professionals; health professionals, via interventions that aim to improve their literacy capacities; and the communication within and accessibility of health systems, via interventions that aim at reducing barriers to access or policies to improve care quality. Guided by the model, we designed a health literacy intervention to be a critical component of the HWePS, comprising a community-wide, multi-channel health information delivery service and individualized self-checkups evaluating a participant’s intrinsic capacity using an evidence-based clinical decision support tool based on the interRAI Check-Up for Self-Report (CUSR) [27].

During the COVID-19 pandemic, delivering valid and reliable information tailored to the community and population’s needs can help promote heath literacy and better communication with the health system [28, 29]. We integrated the five strategies of the comprehensive HL intervention model [21] into the HWePS intervention, facilitating various interactions and communication activities between older people, their families, community lay health leaders (CLHLs; peers), and nurse coaches and other multidisciplinary team members (heath and social professionals). We aim to increase the health literacy of various intervention participants (older people, peers, and health/social professionals) in the low-income urban community as a whole.

## Objectives

Improving health equity in later life should be a top priority of public health officials, especially considering the possibility of extended later life due to increasing longevity and the proportion of older age groups. In order to advance healthy aging for all, it is imperative to reduce health disparities among older people residing in urban, low-income communities in Korea, for which effective community-based health promotion strategies considering social determinants of health are needed. Given the context, this study aims to evaluate whether or not the HWePS, a community-based, multi-level, preventive and integrated elder care model will improve the health and quality of life of older residents in an urban, low-income community, compared to usual-plus care. The HWePS is well-aligned with a nationwide policy goal of building community-based integrated care systems for older people and promoting an aging-in-place policy [30].

## Methods/design

### Study design

The Health and Wellness Program for Seniors (HWePS) is a two-arm, non-randomized, controlled cluster trial that seeks to evaluate a theory-guided, technology-enhanced, integrated health-equity intervention model for older residents in urban, low-income communities in Seoul, Korea, during the COVID-19 pandemic. The HWePS targets complex, multi-level factors influencing disparities, including factors at the individual, interpersonal (social), and community levels [10]. The schedule of enrollment, intervention, and assessment of the intervention is summarized in Fig. 1. A total of two measurements (pre- and post-intervention) are conducted on each individual. A 12-week case management program aiming to build self-care skills and practice with a nurse coach and peer support is rolled out in three clusters and spans an overall study period of approximately 12 months. A community-wide, multi-channel information delivery service aiming to promote heath literacy, and a healthy-living, healthy-aging initiative aiming to build community capacity and resources/networks are continued throughout the entire intervention period. This intervention was developed through a mixed-methods approach guided by 6SQuID [31]; various stakeholders have been involved in developing the heath disparity intervention project, starting with its inception and continuing throughout the entire intervention development process, which will be published as a separate paper. The trial described here is prospectively registered at ISRCTN. This protocol has been reported following TREND guidelines [32].

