#### Primary outcome measure

*Self-rated health* is measured with a single item that asks, “In general, how do you consider your overall health?” using a 5-point scale (1 = Very good; 5 = Very poor). Self-rated health is a widely-used measure of subjective morbidity [39], which has been validated in various settings including for health-equity analyses [40]. *HRQoL* is measured using the Korean version of the EuroQol-5 Dimensions, three-level version (EQ-5D-3L), a widely-used standardized measure of health-related quality of life with good reliability and validity across international samples [41]. The EQ-5D-3L assesses five dimensions of health (mobility, self-care, usual activity, pain/discomfort, and depression/anxiety), and each domain is rated from 1 to 3, with 1 meaning no problems, 2 meaning some problems, and 3 meaning extreme problems.

The primary outcomes will be measured at two time points: at T1 (Week 0; upon enrollment) and T2 (Week 13; following the end of the 12-week personalized intervention period).

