### Sample size and recruitment

This HWePS intervention study is part of a larger community-wide health equity initiative, starting with a community-wide health and wellness survey conducted from November 2020 to January 2021. The sample for the community-wide survey consisted of approximately 700 older adults in the intervention area and 500 older adults in the control area, which is approximately 19.2% and 7.6% of all older adults in each area, respectively (as of October 2020). Informed consent concerning the entire study was obtained by the research team prior to initiating the survey.

The recruitment of participants into the HWePS intervention is based on the roster of older adults who participated in the community survey. The sample size of the HWePS intervention is calculated using the G*Power 3.1.9.2 program as follows. We hypothesize an effect size (as the input parameter for G*Power) of 0.2 based on previous community-based health and wellness interventions for older adults’ self-rated health [57–59]. The required number of samples is identified as 265 for each arm, by choosing the MANOVA approach in two repeated measures (90% power, 5% α error) in two independent groups. With an estimated dropout rate of 30% in the intervention period, a total sample size of approximately 379 participants per arm needs to be recruited.

Enrollment into the study will progress sequentially by clusters based on residents’ *tong* (smaller neighborhood). At the beginning of each intervention period, all individuals in the cluster will be contacted by the research team by telephone and given a brief explanation of the program. We will directly visit the homes for recruitment of those older adults who do not respond to the phone calls due to low technology literacy, wariness, or other reasons. Upon agreeing to participate in the study, the participant will be scheduled for a health survey for baseline data collection by an external assessor. Recruitment and baseline data collection will be simultaneously conducted. Eligibility and consent to participate is reconfirmed by phone or in-person during the intervention recruitment.

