### Assignment of interventions and blinding

Participant assignment into the intervention group or the control group is solely based on area of residence. Participants reside in 15 *tongs* in the intervention area and 15 *tongs* in the control area, and are divided into 3 clusters matched based on mean age and residential type (apartment vs. house).

Considering the nature of the study, limited single-blinding is applied to the intervention, as participants will not be told whether they reside in the intervention or control area, but researchers will be aware of the allocation. Upon giving informed consent, participants in the intervention group will receive an explanation of the entire HWePS intervention, while control group participants will receive an explanation of only the health information component. Assignments will not be explicitly expressed to external assessors but may be inferred throughout the course of the study. An independent data analyst blinded to the assignments will receive a cleaned dataset without any identifiable information.

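### In the second and third clusters T1 precedes care management but not the community initiative, so pooled T1–T2 change leans toward no effect for the whole programme

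*Protocol article*

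**What the plan says.** All references are to the protocol article.

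- **Study design.** Care management "is rolled out in three clusters and spans an overall study period of approximately 12 months". The information service and the healthy-aging initiative "are continued throughout the entire intervention period". For measurement: "A total of two measurements (pre- and post-intervention) are conducted on each individual".
- **Sample size and recruitment.** "Enrollment into the study will progress sequentially by clusters", the clusters being groups of tongs. Contact is also staged: "At the beginning of each intervention period, all individuals in the cluster will be contacted by the research team by telephone". Baseline collection takes place alongside recruitment.
- **Primary outcome measure.** The primary outcomes are taken "at T1 (Week 0; upon enrollment) and T2 (Week 13; following the end of the 12-week personalized intervention period".
- **Assignment of interventions and blinding.** Participants come from 15 tongs in each area and "are divided into 3 clusters matched based on mean age and residential type (apartment vs. house").
- **Intervention (closing summary after Table 1).** The intervention area receives the full package, community initiative included. The control area receives the same information service and nothing else.
- **Objectives; Effect evaluation.** The question is whether the multi-level model as a whole improves health and quality of life, and the primary analysis is described as the effect of the HWePS program, intervention area against control area.

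**The concern.** T1 is labelled pre-intervention. That is right for care management in every cluster. It is right for the programme as a whole only if the community initiative has not yet reached the person. The initiative is described as community-wide and continuous, and nothing in the text stages it by cluster. The three clusters are groups of tongs inside one dong. The remoteness described under Study setting and participants is between the two dongs; no separation between clusters is described.

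If health-education sessions or smartphone education improve self-rated health or EQ-5D before a later cluster enrols, that gain is already in its T1 and drops out of T1–T2 change. Control participants have no matching gain. The pooled contrast then understates the whole-package effect, and a weak or null result could be read as failure of the multi-level model when part of its effect was subtracted at baseline.

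**Working it through.** **1. The plan's own figures.** The dropout step reproduces: 265 / (1 − 0.30) = 378.6, so 379 per arm. The 265 appears from the stated inputs (f = 0.2, two groups, two measurements, noncentral F with λ = f²N and 1 and N − 2 degrees of freedom, power 0.900) as a total N, whereas the plan says per arm. That is a separate matter. The plan's 265 per arm, 530 in total, is used below.

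**2. Delay of T1 after the initiative starts.** Start dates are not in the text. Assume that the initiative begins with cluster 1 and that each cluster needs 13 weeks from T1 to T2.

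- Back to back: T1 at weeks 0, 13 and 26, or 0, 3.0 and 6.0 months.
- Spread evenly with the last T2 at week 52: the last T1 is at 52 − 13 = 39 and the middle one at 19.5, or 0, 4.5 and 9.0 months.

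**3. Share of the effect kept.** Let s be the share of the effect present at T2 that comes from the intervention-area-only initiative (assumed; the document gives no figure). Let g(t) be the initiative's gain after t weeks. A cluster with delay t keeps k(t) = [g(t + 13) − g(t)] / g(t + 13) of that part, so k(0) = 1. With equal clusters:

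pooled share kept = (1 − s) + s × mean k.

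The information service goes to both arms identically and cancels.

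Mean k under three shapes of g:

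- Early step, complete within 13 weeks: (1 + 0 + 0)/3 = 0.333.
- Constant rate, k = 13/(t + 13): back to back (1 + 0.500 + 0.333)/3 = 0.611; spread (1 + 0.400 + 0.250)/3 = 0.550.
- Exponential with a 13-week half-life: back to back (1 + 0.333 + 0.143)/3 = 0.492; spread (1 + 0.215 + 0.067)/3 = 0.427.

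| s | Early step | Constant rate (back to back / spread) | Exponential (back to back / spread) |
|---|---|---|---|
| 10% | 93.3% | 96.1% / 95.5% | 94.9% / 94.3% |
| 25% | 83.3% | 90.3% / 88.8% | 87.3% / 85.7% |
| 50% | 66.7% | 80.6% / 77.5% | 74.6% / 71.4% |

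The loss runs from 100 − 96.1 = about 4% to 100 − 66.7 = about 33%.

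**4. Power.** With 530 in total, √λ = 0.2 × √530 = 4.60, and undiminished power is 99.6%. In the worst cell √λ = 4.60 × 0.667 = 3.07, and Φ(3.07 − 1.96) = Φ(1.11) ≈ 0.87; the noncentral F gives 86.5%. At s = 25% with an early step it gives 96.9%. These values use the plan's own test and take 0.2 as the full effect.

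**The case against.** Several points on the other side stand.

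- **The dates are inferred.** No cluster or initiative start date is in the text. The phrase intervention period is also used per cluster under Sample size and recruitment. If the initiative restarted with each cluster, the problem would vanish. The description of it as community-wide and continuing makes the whole-programme reading the natural one.
- **Not every component acts before T1.** Trained lay leaders support participants after they enrol, and individual referrals go through the care team. That benefit mostly stays inside T1–T2. Direct exposures such as education sessions and smartphone education are what remain. The Discussion also concedes limited resources for the initiative, so the upper end of the assumed range has no particular support.
- **Model terms may be left to an analysis plan.** The absence of a cluster term from the article is not a fault in itself. If matched clusters enrol together in both areas, pandemic conditions are balanced between arms.

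Three stronger readings are tempting and are not supported.

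- A reader might infer that power falls from 90% to 77% or 58%, using Φ(3.242 × share − 1.96) with shares of 83% and 67%. That needs a sample giving exactly 90%, which is 265 in total, not the stated 265 per arm. The assumed 0.2 may also already be a T1–T2 effect.
- A reader might count a further loss because 13 weeks captures only part of a gain building over 12 months. That comes from the follow-up horizon and affects cluster 1 equally; it is not caused by late baselines.
- A reader might replace T1 by the late-2020 survey. The article does not show that the items match. That survey ran from November 2020 to January 2021 and the trial was registered in September 2021, so the gap to follow-up would be long and would differ by cluster.

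**Conclusion.** The point holds as a mismatch between what is measured and what is claimed. For the second and third clusters, T1 is before care management but, on the natural reading, not before the programme. If the initiative helps people directly before they enrol, pooled T1–T2 change is biased toward no effect for the whole-package question.

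The size is unknown. A loss of about 4% to 33% rests on assumed community shares of 10% to 50%, three equal clusters, an initiative starting with cluster 1, and a contrast built on change from T1. A model that adjusts for T1 with a coefficient below 1 would remove less. The loss is zero if the initiative reaches nobody before enrolment. Power is not the main harm, since it stays at about 86% or more with 265 per arm. What is at stake is what a positive, weak or null result may be said to show.

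**What to change.** No new data are needed.

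1. State that pooled T1–T2 estimates the added effect of the 12-week care management, together with 13 weeks of the initiative, on top of a community initiative already running. It does not estimate the full programme effect.
2. Include matched cluster (wave) and wave-by-time in the primary model. The matched clusters already exist in both areas. These terms absorb conditions that differ between waves; they do not restore gains made before T1.
3. Pre-specify the arm-by-time effect by wave as a sensitivity analysis, with cluster 1 named as the contrast closest to a pre-programme baseline.
4. Give in the text the start of the initiative and of each cluster, so that the delay can be read off.

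**Cost.** Wording and a few model terms. The cluster-1 estimate uses about a third of the sample, 265/3 ≈ 88 per arm, so its standard error is about √3 = 1.73 times the pooled one. Differences between waves should be read descriptively, because they also carry changes in pandemic conditions and in how the programme was delivered.
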